**Session 1**
SquatsBiceps curlSuperman in quadrupedDumbbell chest press in horizontal planeShoulder rotators with elastic bandDumbbell rowing
**Session 2**
Proprioceptive shoulder exercises with ball on wallStatic strideUpper limb flexion with ball on wallIsometric abduction with ball (elbow 90º)Prone spine extensionQuadruped hip abduction
**Session 3**
Dumbbell triceps extensionQuadruped gluteal kickTriceps kick with dumbbellLateral shoulder raises with dumbbellsDead weight with dumbbellsRowing with elastic band

### Data Management and Analysis

Once all the measurements included in the measuring instruments section have been taken, they will be recorded and analyzed using SPSS (version 28.0; IBM Corp) [52].

The quantitative data of the sample will be described by number, mean, and SD.

A result is understood to be significant when *P*≤.05. In statistics, significance or internal consistency indicates that there is congruence between the different results obtained [53].

For the statistical analysis of the results of this test, 2 tests will be performed as follows.

Repeated measures ANOVA: This analysis allows us to evaluate whether the differences between the results of the same test in a participant are statistically significant. If so, it also determines what percentage of the effect is attributable to the intervention and not to other factors [53]. Two ANOVA analyses will be performed: one comparing the preintervention assessment with the postintervention assessment, and the other comparing the postintervention with the assessment 12 weeks later. This test will check if there is a significant improvement in the different measures of pain, physical function, and quality of life. Finally, the paired comparison table will tell us in which measurement periods the differences are found [53].ANOVA of differences: In this case, the differences between the results of the intervention group and the control group will be compared [53]. With the results obtained from this statistical analysis, it will be possible to verify whether the differences between groups in terms of pain, physical function, and quality of life are significant between the participants receiving the intervention and those belonging to the control group.MANOVA: To assess the overall effect of the intervention and determine whether the hypotheses can be accepted or refuted, the following hypotheses will be tested [53].

These statistical analyses described the significance between the test results of the same individual and the significance between the different results of both groups of the test that will be tested.

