### Study Design

This study will be a single-blind, randomized clinical trial. To determine the efficacy of a therapeutic exercise program on the different dimensions of quality of life, physical function, and pain in patients with cancer. Once the participants have been recruited, they will be randomly assigned to 2 groups (intervention group and control group). Three assessments will be made: initial assessment, assessment after the end of the intervention, and assessment 12 weeks after the end of treatment. The intervention group will follow a 12-week therapeutic exercise plan, and the control group will follow the usual recommendations for this type of patient. After this last assessment, the participants in the control group will be offered the intervention. (Figure 1). Approval will be sought from the ethics committee of the University Hospital of Torrecárdenas.

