### Study Population

The participants will be recruited through the oncologists of the University Hospital of Torrecárdenas. The inclusion criteria will be the following: women aged between 45 and 65 years (age range with the highest incidence in Spain), with oncologic treatment completed less than 3 months ago, without metastasis, without pathologies that contraindicate exercise, and who have agreed to sign the informed consent form. The exclusion criteria will include: not attending scheduled sessions to instruct on the exercises to be performed, being part of other studies, undergoing another type of therapy, and pregnant patients.

The selected age range of 45 to 65 years for participants is based on epidemiological data indicating that this demographic encompasses the highest incidence of breast cancer in Spain. This range ensures a representative sample for evaluating the intervention's efficacy while excluding populations less likely to face similar diseases and treatment dynamics. Additionally, menopause is included as an independent variable in the analysis due to its significant influence on both physiological and psychological responses to breast cancer treatment and exercise interventions. Hormonal changes associated with menopause can affect musculoskeletal health, fatigue levels, and overall quality of life, making it a critical factor to consider when evaluating the intervention’s outcomes on pain, physical function, and quality of life [31]. By accounting for these variables, the study aims to provide a nuanced understanding of how menopausal status may modulate the benefits of supervised exercise in patients with cancer.

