### Sample

To calculate the sample size, the QuestionPro software (QuestionPro Inc) was used [32]. It consists of software that, among other functions, incorporates a sample calculator for research.

Based on breast cancer morbidity data in the province of Almeria for 2022, published by the National Institute of Statistics [33], the calculation assumed a moderate effect size of 0.5, based on prior research on exercise interventions in similar populations. To ensure sufficient sensitivity to detect meaningful differences, the significance level (α) was set at .05 (2-tailed), and the study power (1–β) was set at 80%. Considering these assumptions, an initial sample size of 280 participants was determined. However, recognizing the potential for participant dropout, which is common in exercise-based trials, we accounted for an estimated attrition rate of 15%. To compensate for this and maintain statistical power, the final sample size was adjusted to 325 participants.

This approach ensures that the study is adequately powered to detect significant differences between the intervention and control groups for the primary outcomes. If further specifics or expanded parameters are required, we are happy to provide additional details. This explanation aims to address editorial concerns and clarify the robustness of our calculation methodology.

In the beginning, an attempt will be made to recruit the estimated size of participants; if this cannot be done, a smaller sample size will be used, assuming a decrease in the confidence level of the results.

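### The arms are compared by an undefined ANOVA of differences without baseline as a covariate, and no listed analysis contains menopausal status

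*Protocol article*

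**What the plan says.** Study Design sets the visits: "Three assessments will be made: initial assessment, assessment after the end of the intervention, and assessment 12 weeks after the end of treatment". The Abstract confirms that pain, physical function and quality of life are each measured at all three.

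Data Management and Analysis then lists three kinds of analysis:

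- Repeated-measures ANOVA, run twice: "one comparing the preintervention assessment with the postintervention assessment, and the other comparing the postintervention with the assessment 12 weeks later".
- A between-arm test: "ANOVA of differences: In this case, the differences between the results of the intervention group and the control group will be compared".
- A MANOVA for the overall effect, with no list of the outcomes that enter it.

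No covariate is named for any of them.

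Study Population states that "menopause is included as an independent variable in the analysis", and gives as an aim to learn "how menopausal status may modulate the benefits of supervised exercise in patients with cancer". The analysis section does not mention menopause.

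**The concern.** There are three linked points.

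1. **The between-arm contrast is not defined.** The differences could be changes from baseline compared between arms, or raw scores at a later visit compared between arms. The two have different variances, and the article does not choose.

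2. **Baseline is not a covariate under either reading.** The measurement is already paid for, so the precision it would add to the treatment estimate is given up at no saving. The follow-up visit is served least well. The Hypothesis section claims that benefit lasts at least 12 weeks after the programme, but the second repeated-measures ANOVA runs only from the post-intervention visit to follow-up. It shows whether scores moved after treatment ended and gives no baseline-adjusted arm difference at follow-up.

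3. **Menopause is announced but not modelled.** A question about whether menopausal status changes the benefit of exercise needs a term for arm by menopausal status, and no listed test has one. If this stays open, whether and how to use the variable can be decided after the data are seen.

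**Working it through.** **The plan's own figure.** Sample gives an effect size of 0.5, two-sided alpha 0.05, 80% power and 280 women before dropout. Randomization gives 1:1 allocation, so 140 per arm. A two-sample comparison of means on those inputs needs 63 per arm, 126 in total, by the normal approximation (64 per arm, 128 in total, by the t-test). The stated 280 therefore does not reproduce. That is a separate matter, but it means that 280 evaluable women carry more power than the stated 80%.

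**Variances.** Take an outcome variance of 1 at each visit and in each arm, and let r be the correlation between baseline and later score. The article does not give r, so 0.3, 0.5 and 0.7 are assumptions.

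- Raw score: 1
- Change score: 2(1 − r)
- Baseline-adjusted (ANCOVA): 1 − r²
- Adjusted relative to change: (1 − r²) / [2(1 − r)] = (1 + r)/2
- Adjusted relative to raw: 1 − r²

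| r | Raw | Change | Adjusted | Adjusted / change | Adjusted / raw |
|---|---|---|---|---|---|
| 0.3 | 1 | 1.40 | 0.91 | 0.65 | 0.91 |
| 0.5 | 1 | 1.00 | 0.75 | 0.75 | 0.75 |
| 0.7 | 1 | 0.60 | 0.51 | 0.85 | 0.51 |

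The ordering does not depend on equal variances. Each method analyses the later score minus b times baseline. A raw-score test fixes b at 0 and a change-score test fixes it at 1, whereas ANCOVA estimates the b that minimises the variance.

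The undefined wording matters too: change scores have 40% more variance than raw scores at r = 0.3 and 40% less at r = 0.7.

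**Interval width at 140 per arm.** The 95% half-width is 1.96 × √(2v/140), in outcome SDs, with v taken from the table.

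| r | Raw | Change | Adjusted |
|---|---|---|---|
| 0.3 | 0.234 | 0.277 | 0.223 |
| 0.5 | 0.234 | 0.234 | 0.203 |
| 0.7 | 0.234 | 0.181 | 0.167 |

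**Power at 140 per arm, effect 0.5 outcome SDs.** Power is Φ(0.5/√(2v/140) − 1.96).

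| r | Raw | Change | Adjusted |
|---|---|---|---|
| 0.3 | 98.7% | 94.2% | 99.2% |
| 0.5 | 98.7% | 98.7% | 99.8% |
| 0.7 | 98.7% | 99.97% | >99.9% |

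Every entry exceeds 80%.

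**Smaller trial.** Sample allows a smaller number if recruitment falls short. As an assumed illustration, take 50 evaluable per arm. The raw-score test has Φ(0.5/√(2/50) − 1.96) = Φ(0.54), about 70%. With adjustment at r = 0.5 it is Φ(2.5/√0.75 − 1.96) = Φ(0.93), about 82%.

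**Repeated-measures route.** If arm is meant as a between-subject factor in the first ANOVA, its arm-by-time test with two visits is the same as the change-score test, so the change column applies.

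**Menopause.** No association between menopausal status and any outcome is given, so no gain from adding it can be calculated. Here the check is only that Study Population announces the variable and the list of tests lacks it.

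**The case against.** The best defence is that comparing change scores, or raw scores, is a valid test in a randomised trial. Over repeated randomisations both are unbiased, so ANCOVA is better practice and not the correction of an error. Covariate lists are often left to an analysis plan, and none is shown here. At the stated sample size the trial has power to spare. On menopause, the analysis section is silent and does not deny what Study Population says.

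Much of this stands, and it rules out several stronger readings that a reader might infer:

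- **That the plan ignores baseline.** It does not. The first repeated-measures ANOVA uses baseline as a repeated level, and so does a change-score reading of the between-arm test. What is missing is baseline as a covariate.
- **That the analysis is complete-case.** The article states no missing-data rule. This would be an inference from procedure names, and such rules are commonly set elsewhere.
- **That 15% attrition means about 49 women (325 × 0.15 = 48.75) would be recovered by a mixed model.** The 15% is not split by visit. The two ANOVAs are run separately, so a woman who misses only follow-up stays in the first. A mixed model of post-baseline scores also excludes women who have none. The number recovered is unknown.
- **That chance imbalance biases the comparison.** An observed imbalance matters conditionally, but randomisation keeps both comparisons unbiased overall.
- **That leaving out menopause costs a known amount of precision.** No figure supports this, and the article motivates the variable largely as a modifier of benefit.

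The defence does not remove the core. The article goes beyond silence: it lists its tests, the between-arm one is ambiguous, and under either meaning a more precise analysis uses data already collected. It also announces a menopause question that the listed tests cannot answer.

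**Conclusion.** The point holds as a recommended improvement to a stated method, together with a mismatch between two sections that needs reconciling. For r between 0.3 and 0.7, adjustment cuts variance by 35% to 15% relative to change scores and by 9% to 49% relative to raw scores. At r = 0.5 either gain equals 1/0.75 = 1.33 times the patients. These sizes rest on assumed correlations, equal variances at the visits and large-sample formulas; the direction rests only on the last. At 280 evaluable women and an effect of 0.5, the result is narrower intervals and not rescue of power. The gain would count for more if recruitment fell well short. The menopause mismatch needs no assumption, but its statistical cost cannot be sized.

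**What to change.** For each outcome, replace the ANOVA of differences with one of these:

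- an ANCOVA at each post-baseline visit, with arm and the baseline score; or
- one mixed model of the post-intervention and 12-week scores, with arm, visit, arm-by-visit, baseline and baseline-by-visit, using all women with any post-baseline value.

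Report the arm difference with its 95% confidence interval at both visits. The follow-up estimate then bears directly on the hypothesis of lasting benefit.

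Reconcile Study Population with Data Management and Analysis by adding menopausal status as a covariate and an arm-by-menopause interaction, labelled exploratory and reported with a confidence interval.

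The cost is revised wording and a little more programming in the planned SPSS. Menopausal status takes one baseline question. Design, visits and sample size are unchanged.

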## Methods

### Hypothesis

A supervised exercise program reduces pain and improves physical function and quality of life in female patients with cancer compared to a control group not receiving the exercise program.The beneficial effects of the supervised exercise program are maintained over time at least 12 weeks after the end of the program.

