### Measuring Tools for Evaluation

#### Disability of the Arm, Shoulder, and Hand Questionnaire

Self-administered and validated questionnaire in Spanish, the original questionnaire was first published in 1996 [35]. This measuring instrument assesses the impact of processes occurring in the upper limb. This questionnaire consists of 30 items and 2 optional modules. The score obtained is transformed to a scale from 0 to 100, where higher scores show a worse result. It shows a high internal consistency (Cronbach α=0.96) [36].

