## Discussion

### Principal Findings

This randomized clinical trial is intended to test the efficacy of an exercise program applied to patients with cancer.

Most of the patients present a deterioration of their quality of life and physical function after suffering breast cancer, physical exercise can be a great ally to counteract these negative effects [23-30]. Therefore, the results obtained in the intervention group are expected to be significantly better than those of the control group. It is likely that there will be benefits to the intervention in some aspects and not in all the variables measured in the study. In addition, the benefits provided are expected to be maintained in the long term, hence the reassessment 12 weeks after the end of the intervention.

A compelling finding emerges from the systematic review by Montaño-Rojas et al [48], which demonstrates significant muscle strengthening benefits, even with low-intensity and short-duration exercise programs. Participants in these programs showed notable improvements in muscle strength compared to those who did not engage in physical activity. This aligns with the meta-analysis by Shen et al [54], which reported improvements in pain and joint amplitude of the upper limb following physical exercise after radiotherapy in breast cancer. These findings complement international guidelines, such as those from the Clinical Oncology Society of Australia (COSA), which recommend at least 150 minutes of moderate aerobic exercise and 2 resistance training sessions per week, tailored to the individual’s health and treatment phase. Like the protocol in this study, COSA highlights the benefits of exercise in reducing fatigue, improving musculoskeletal health, and enhancing quality of life [30]. However, COSA also emphasizes the routine integration of exercise into oncology care, a practice that remains inconsistently implemented across European health care systems. This comparison underscores the universal importance of exercise in patients with cancer and highlights the need for tailored adaptations to local health care systems and cultural contexts to maximize accessibility and impact [29].

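### The MANOVA that decides the hypotheses cannot confirm a three-part directional claim, and the primary outcomes the plan relies on are never named

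*Protocol article*

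**What the plan says.** The Hypothesis section joins three domains and gives each a direction: "A supervised exercise program reduces pain and improves physical function and quality of life in female patients with cancer compared to a control group". A second hypothesis says that the benefit lasts at least 12 weeks after the program ends.

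Data Management and Analysis lists repeated measures ANOVAs (baseline to post-intervention, and post-intervention to 12 weeks later), an ANOVA of differences between the arms, and a MANOVA. The MANOVA is there "To assess the overall effect of the intervention and determine whether the hypotheses can be accepted or refuted". The sentence goes on to say that "the following hypotheses will be tested", but none is listed after it, so the ones in the Hypothesis section are the only candidates. The threshold is general: "A result is understood to be significant when *P*≤.05". Nothing makes the univariate tests depend on the MANOVA result.

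The Sample section says the study is "adequately powered to detect significant differences between the intervention and control groups for the primary outcomes". No outcome, scale or time point is called primary anywhere in the article. The Discussion expects a split result: "It is likely that there will be benefits to the intervention in some aspects and not in all the variables measured in the study".

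The instruments do not share a direction. For the arm, shoulder and hand questionnaire, "higher scores show a worse result", while the QLQ-C30 is described as scoring higher for better quality of life.

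**The concern.** The MANOVA null hypothesis is that the two mean vectors are equal. Rejecting it says that at least one linear combination of the outcomes differs. It does not say which outcome, how many outcomes, or in which direction. The hypothesis it is meant to settle needs all three domains to move the right way. The deciding test and the claim therefore do not match, and a movement in one domain could be reported as confirming the whole hypothesis. The Discussion already treats a partial result as likely, and the plan does not say what such a result would mean for the hypothesis.

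The unnamed primary outcomes make this worse. With no scale and visit fixed, and every univariate result called significant at the same threshold, the result to be emphasised can be chosen after the data are seen. Later analysis cannot repair that.

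**Working it through.** **Inputs.** From the article: 280 participants before attrition and 1:1 allocation, so 280/2 = 140 per arm; two-sided alpha .05; effect size 0.5, read as a standardised mean difference. Assumed, because the article gives no values: equal correlations between outcomes, and shifts of 0.4 SD and 0.3 SD. The article states no error rate or power for the MANOVA, so there is no figure of its own to reproduce on this point. The 280 is taken as given. An effect of 0.5 with 80% power gives 126 in total, not 280, but that is a separate matter.

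**1. How often the MANOVA rejects when one outcome moves.** With two groups the MANOVA is Hotelling's T². For p outcomes with common correlation ρ and a shift δ in one outcome only:

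D² = δ²[1+(p−2)ρ] / {(1−ρ)[1+(p−1)ρ]}, noncentrality λ = (n/2)D², referred to F with p and 2n−p−1 degrees of freedom.

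| p | ρ | D² for δ = 0.4 | λ = 70·D² | Rejection |
|---|---|---|---|---|
| 3 | 0.3 | 0.16×1.3/(0.7×1.6) = 0.186 | 13.0 | 87% |
| 3 | 0.5 | 0.16×1.5/(0.5×2.0) = 0.240 | 16.8 | 94% |
| 22 | 0.3 | 0.16×7.0/(0.7×7.3) = 0.219 | 15.3 | 57% |
| 22 | 0.5 | 0.16×11/(0.5×11.5) = 0.306 | 21.4 | 76% |

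The shift enters as δ², so a worsening of 0.4 SD gives exactly the same figures. With p = 3, one outcome better by 0.4 SD and another worse by 0.3 SD, rejection is 99% (ρ = 0.3) or above 99.9% (ρ = 0.5).

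**2. Scale count.** The 22 is a count from the instrument descriptions: arm, shoulder and hand questionnaire 1; pain questionnaire 2; QLQ-C30 10; QLQ-BR23 6; 1-RM 3 (each arm and the leg press). Without 1-RM it is 19. The article does not say that every scale will be tested.

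**3. Univariate tests with no true effect.** The chance of at least one P≤.05 among k independent tests is 1−0.95^k. The correlated figures use k equally correlated normal test statistics.

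| k, one contrast | ρ = 0.7 | ρ = 0.5 | independent |
|---|---|---|---|
| 3 outcomes | 11% | 13% | 14% |
| 4 questionnaires | 13% | 16% | 19% |
| 22 scales | 30% | 44% | 68% |

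Counting only false results in the favourable direction, the range from ρ = 0.7 to independence is 5% to 7% for three outcomes, 7% to 10% for four, and 15% to 43% for 22. The MANOVA, taken alone, is a single test at 5%.

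**4. Power of rules that match a stated claim (140 per arm, d = 0.5).**
- One outcome at two-sided .05: 0.5×√(140/2) = 4.18, and 4.18−1.96 = 2.22, so power is 98.7%.
- All three domains at .05, independent: 0.987³ = 96%.
- One domain at .05/3 = .0167, the strictest Holm step: 96%.
- The all-three rule at smaller sizes, independent: 80% at 94 per arm and 51% at 63 per arm.

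**The case against.** The strongest reply is that a MANOVA is itself a control on multiplicity. Taken alone it keeps a 5% global error, so under the stated deciding rule a false acceptance by chance is no more likely than in any single test. This stands. The inflation belongs only to the ungated univariate tests, which are a reporting risk and not the false-success rate of the accept/refute rule.

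A reader might infer that the trial would very probably find a success by chance. The article does not support that. The high figures need all 22 scales to be tested, and the 22 is a count from the instrument descriptions. The abstract ties the three domains to four questionnaires, for which the range is 13% to 19%. The 1-RM measures appear in neither the abstract's outcome list nor the hypothesis.

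A reader might also infer that plain harm would be declared a success. The MANOVA does ignore sign, but the hypothesis states direction, the repeated measures ANOVA is meant to look for improvement, and the arms are compared directly, so a clear worsening would be seen. The realistic danger is a mixed or single-domain result read as confirming everything.

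The Discussion sentence on partial benefit is an expectation, not a decision rule. It shows only that the unresolved case is foreseen.

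Detailed multiplicity procedures may sit in an analysis plan that is not shown, and their absence here is not the point. The article itself fixes the deciding test and the threshold, and it claims power for primary outcomes that it does not identify.

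**Conclusion.** The concern holds in this form: the test chosen to decide the hypotheses cannot establish the claim it is meant to decide, and the primary outcomes on which the power statement rests are not named. With three outcomes and 140 per arm, a 0.4 SD movement in one outcome alone triggers rejection 87% to 94% of the time, in either direction; with 22 scales entered it is 57% to 76%. The univariate inflation is real but modest for three or four outcomes. It becomes large, 30% to 68%, only if every described scale is tested.

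These sizes rest on assumed equal correlations (0.3 to 0.5 for the MANOVA, 0 to 0.7 for the univariate tests), an assumed 0.4 SD shift, and 280 completers. The mismatch between test and claim depends on none of them.

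**What to change.** Name one scale for each of pain, physical function and quality of life at the post-intervention visit as primary, compared between arms. Remove the accept/refute role of the MANOVA; it can stay as a descriptive summary. Then choose a rule that fits the claim:

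- **To support the three-part hypothesis:** require all three domains to favour the intervention, each at two-sided .05. No alpha split is needed.
- **To allow a narrower claim:** name a single primary outcome, or apply Holm across the three domains, and limit the conclusion to what passes. Neither option tests the joint hypothesis, so its wording would have to change.

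Test the 12-week follow-up contrast next in a fixed sequence. Report all other scales and 1-RM as secondary, with confidence intervals. List the hypotheses that the analysis section announces, and check that the trial registration names the same primary outcomes.

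The cost is wording, a small loss of power and a narrower permitted claim. At 140 per arm and d = 0.5, power is about 96% for the all-three rule (if the domains are independent) and 96% for the strictest Holm step, against 98.7% for one outcome. These figures need 280 completers. The Sample section allows a smaller sample, and the all-three rule falls to 80% at 94 per arm, so the choice should be made with likely recruitment in view and before any outcome data are seen.
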